# Electroacupuncture for Menstrual‐Related Migraine: Protocol for a Multicenter Single‐Blinded Randomized Controlled Trial

**DOI:** 10.1155/prm/2200276

**Published:** 2026-07-20

**Keywords:** electroacupuncture, menstrual-related migraine, multicenter randomized controlled trial, protocol

## Abstract

**Importance:**

Menstrual‐related migraine (MRM) is a prevalent neurological condition affecting females, with prolonged duration, severe symptoms, and poor drug response, significantly impairing their quality of life. Electroacupuncture shows promise as a nonpharmacological intervention for migraine. However, there is a deficiency in high‐quality evidence‐based research assessing its efficacy in MRM. To address this gap, we present a detailed protocol to evaluate electroacupuncture’s therapeutic effects in MRM.

**Methods and Analysis:**

A total of 120 participants with MRM will be randomly divided into two groups (1:1): the electroacupuncture group and the sham electroacupuncture group. Participants will receive 30‐min treatments (electroacupuncture or sham) for 6 sessions every 4 weeks (18 sessions over 12 consecutive weeks). The primary outcome will be migraine days and attacks during Weeks 9–12 vs. baseline. Secondary outcomes (all vs. baseline unless specified) include the following: (1) frequency‐related: migraine days/attacks per 4 weeks (Weeks 1–24, excluding Weeks 9–12; and during menstrual/nonmenstrual periods). (2) Symptom characteristics: days/attacks with migraine‐associated symptoms and attack duration per 4 weeks. (3) Patient‐reported: visual analog scale (VAS), Migraine Disability Assessment (MIDAS) questionnaire, Insomnia Severity Index (ISI), Generalized Anxiety Disorder‐7 (GAD‐7), and Patient Health Questionnaire‐9 (PHQ‐9). (4) Others: treatment response rate, average dosage, and frequency of emergency drugs. All adverse events during the research will be documented. SAS 9.4 statistical software will be used for analyses.

**Trial and Dissemination:**

Ethical approval was obtained from the Medical Ethics Committee of LongHua Hospital Shanghai University of Traditional Chinese Medicine (No. 2024LCSY150), Shanghai Gongli Hospital of Pudong New Area (GLYY1s2024‐085), and Shanghai Municipal Hospital of Traditional Chinese Medicine (2025SHL‐KY‐60‐01), and the study was registered with the International Traditional Medicine Clinical Trials Registry. All participants who fulfill the inclusion criteria and consent to join the study will sign a written informed consent form before randomization.

**Trial Registration:** International Traditional Medicine Clinical Trials Registry: ITMCTR2024000795

## 1. Introduction

Migraine is a common neurological disease with an incidence rate ranging from 10% to 20% [1], which in females is two times that in males [2]. More than 50% of migraines are associated with menstruation in female patients [3]. Nearly 14% of female patients suffer from migraine only during the menstrual period, referred to as pure menstrual migraine (PMM), while 60% of them experience migraine both in menstrual and nonmenstrual periods, known as menstrual‐related migraine (MRM) [4]. Compared with PMM, there is usually no prodrome before an MRM attack, but it has a longer duration and more severe associated symptoms such as pain, nausea, vomiting, photophobia, and phonophobia [5]. MRM has a worse response to treatment and can easily recur. Among people under 50 years old, migraine is the primary cause of reduction of quality of life and functional impairment [6] and leads to clinical symptoms such as anxiety, depression, and insomnia [7]. Among women of reproductive age, 35%–54% suffer from MRM and report higher Migraine Disability Assessment (MIDAS) scores [8], indicating greater impairment in daily work, family life, and social participation [9]. Menstrual‐related symptoms, including MRM, cause about 9 days of annual productivity loss per person [10], which costs further add to personal and societal economic burdens.

The main therapy for MRM is staged drug treatment, including nonspecific treatment, such as nonsteroidal anti‐inflammatory drugs, nonopioid analgesics, and caffeine analgesic combinations (e.g., aspirin acetaminophen + aspirin + caffeine) for the acute phase and specific treatment for the acute phase using triptans, ergotamine, ergotamine derivatives, and gepants. For menstrual migraine (MM), short‐term prevention use of triptans or other agents may also be considered [11]. However, the therapeutic effects are not as expected due to adverse reactions such as dizziness, nausea, and gastrointestinal discomfort caused by drugs and migraine due to frequent overdoses [12]. A prospective cohort study of 500 participants showed that triptan use was associated with higher recurrence frequency and longer attack duration in patients with MRM. This suggests that increased triptan use may further elevate the risk of medication overuse [13]. Treatment of MRM has become an important public health issue, which is worth our active exploration for therapies to relieve pain in patients.

Previous studies have confirmed the clinical efficacy of acupuncture treatment for migraines, which can significantly reduce seizure frequency and the number of days with migraine [14]. In 50% of patients, the frequency of migraine is at least halved after acupuncture treatment, and the effect is more obvious than prophylactic treatment [15]. In addition, the adherence of patients receiving acupuncture treatment is better, and there is less interruption in clinical trials because of adverse reactions [16]. However, a systematic review of 826 participants showed that acupuncture was not superior to sham acupuncture in reducing monthly MM frequency, attack duration, average headache intensity, or analgesic use [17]. Although a recent systematic review reported that acupuncture reduced visual analog scale (VAS) scores, attack frequency, and duration in MM, the GRADE certainty of evidence was rated as low, and substantial heterogeneity was observed across pooled analyses [18]. Therefore, acupuncture cannot be recommended for MM until more robust evidence becomes available. In addition, reviewing the clinical evidence of treatment for MRM, there is only one monocentric RCT that found that both acupuncture and sham acupuncture can reduce MRM attacks but with no significant differences [19]. The significance of existing clinical guidance on the efficacy of electroacupuncture for MM is limited, and no definitive conclusions can be drawn [17, 20]. Consequently, high‐quality evidence‐based research is needed to validate the clinical effectiveness of electroacupuncture in treating MRM.

To further assess the clinical effectiveness and security of electroacupuncture treatment for MRM and establish an objective scientific basis, we designed a multicenter, randomized, controlled, single‐blind study. This study aimed to assess the clinical efficacy and safety of electroacupuncture in treating MRM by providing a comprehensive evaluation of migraine symptoms in patients with MRM compared with sham electroacupuncture. We hypothesized that after 12 weeks of electroacupuncture treatment, there would be a significant reduction in migraine symptoms among MRM patients, thereby decreasing their reliance on pain medication. The goal of this study was to provide robust evidence for the clinical efficacy of electroacupuncture in treating MRM and serve as a reference for developing treatment strategies for this condition.

## 2. Patients and Methods

### 2.1. Setting

We conducted a multicenter, randomized, single‐blind, controlled clinical trial across three centers in China: LongHua Hospital Shanghai University of Traditional Chinese Medicine, Shanghai Gongli Hospital of Pudong New Area, and Shanghai Municipal Hospital of Traditional Chinese Medicine, Shanghai University of Traditional Chinese Medicine. We will recruit participants and conduct treatment in these three hospitals. Ethical approval was obtained from the Medical Ethics Committee of LongHua Hospital Shanghai University of Traditional Chinese Medicine (No. 2024LCSY150), Shanghai Gongli Hospital of Pudong New Area (GLYY1s2024‐085), and Shanghai Municipal Hospital of Traditional Chinese Medicine (2025SHL‐KY‐60‐01), and the study was registered with the International Traditional Medicine Clinical Trials Registry. A total of 120 MRM participants will be recruited for this trial and assigned to the electroacupuncture or sham electroacupuncture groups in a 1:1 ratio. The recruitment period will be from December 2024 to May 2027. A flowchart of the trial procedure is shown in Figure 1. This study adheres to the Declaration of Helsinki.

**FIGURE 1 fig-0001:**
[figure not shown]
Trial flow chart. MIDAS, Migraine Disability Assessment; VAS, visual analog scale; ISI, Insomnia Severity Index; GAD‐7, Generalized Anxiety Disorder‐7; PHQ‐9, Patient Health Questionnaire‐9.

### 2.2. Participants

Participants will be eligible for inclusion if they meet the following inclusion criteria: (1) meet the diagnostic criteria for MRM without aura according to the International Classification of Headache Disorders (ICHD‐3); (2) female aged 18–50 years; (3) the courses of MRM without aura last more than 12 months [21]; (4) the frequency of migraine attack is 2–8 times on average and occurrences less than 15 days in one month within 3 months before enrollment [21]; (5) with regular menstrual cycle; and (6) agree to participate in this study and complete the signing of informed consent. Informed consent will be obtained from all participants prior to inclusion.

Participants will be excluded if they meet any of the following criteria: (1) the presence of other types of primary or secondary headache; (2) a combination of severe cardiovascular and cerebrovascular, neurologic, hematological, and acute infectious diseases; (3) active or previous history of peptic ulcer disease, gastrointestinal bleeding, or perforation; (4) use of preventive migraine medicine within the 3 months prior to the screening; (5) planned pregnancy during the treatment period, oral contraceptive distribution, or during the period of pregnancy or lactation; (6) those who had received acupuncture treatment within 1 year [22]; (7) with cardiac pacemakers; and (8) with metal allergy or serious fear of needle. All participants who fulfill the inclusion criteria and consent to join the study will sign a written informed consent form.

### 2.3. Interventions

The participants will be randomly assigned to the electroacpuncture and sham electroacupuncture groups in a 1:1 ratio. All participants will receive 6 sessions every 4 weeks (twice a week in the week before and during the menstrual period, once a week for the remaining 2 weeks), each lasting for 30 min. The participants will receive 18 sessions in total for 12 consecutive weeks and a follow‐up period of 12 weeks.

If participants had suffered from severe pain (VAS > 8 [16]), oral ibuprofen sustained‐release capsules (trade name: ibuprofen sustained‐release capsules, 300 mg, Shanghai Xinyi Tianping Pharmaceutical Co.) were allowed under the guidance of the doctor. The initial dose is 300 mg/day, and the dosage can be adjusted according to the situation; however, the maximum daily dose does not exceed 800 mg [23]. The dosage, time, and reaction to medicine will be recorded in detail in a case report form (CRF). If the patient has taken medication within the 12 h preceding the efficacy assessment, the evaluation should be postponed for a duration of 24 h.

#### 2.3.1. Electroacupuncture Group

Participants in the electroacupuncture group will be treated with acupuncture at obligatory acupoints, including GV20, GV24, CV4, EX‐HN5 (bilateral), LU7 (bilateral), and SP6 (bilateral). According to the meridian diagnosis and the location of the headache in the acute attack, additional acupoints will be selected: LI4 (bilateral) and ST8 (bilateral) for Yangming migraine (pain predominantly in the forehead, supraorbital ridge, and nasal root); LR3 (bilateral) and PC6 (bilateral) for Jueyin migraine (pain predominantly at the vertex of the head); GB8 (bilateral) and GB34 (bilateral) for Shaoyang migraine (pain predominantly on the side of the head); and SI3 (bilateral) and BL9 (bilateral) for Taiyang migraine (pain predominantly in the occipital region or radiating downward to the nape). Details of the acupoint position and acupuncture technique are shown in Table 1 and Figure 2. (Acupoint location: refer to The Location of Acupoints: State Standard of the People’s Republic of China [GB/T 12346–2021]). Participants will be placed in the supine position, and all acupoints will be routinely disinfected. The acupoints will be treated with balanced tonification and purging manipulation to achieve the Deqi sensation with feelings of soreness, numbness, heaviness, and distension through techniques such as lifting, thrusting, and twisting. A disposable acupuncture needle (Suzhou Medical Supplies Factory Co., Hua Tuo, China) will be selected as the acupuncture tool. Electroacupuncture treatment will be conducted in the form of dense and sparse waves using the HANS acupoint nerve stimulator (model LH 200A; Nanjing Jisheng Medical Technology Co. Nanjing, China), connecting GV20 to the left EX‐HN5 and GV24 to the right EX‐HN5. The electroacupuncture frequency was set at 2/100 Hz, with intensity adjusted to the patient’s comfort [24].

**TABLE 1 tbl-0001:** The location and manipulation of acupoints in the electroacupuncture group.

Acupoint	Location	Manipulation
GV20 (Baihui)	On the anterior midline of the head. This acupoint is found 5 cun superior to the anterior hairline.	The needle is inserted horizontally by 0.5–0.8 cun.
GV24 (Shenting)	On the anterior midline of the head. This acupoint is found 0.5 cun superior to the anterior hairline.	The needle is inserted horizontally by 0.3–0.5 cun.
CV4 (Guanyuan)	On the anterior midline of the abdomen. This acupoint is found 3 cun inferior to the center of the umbilicus.	The needle is inserted vertically by 1.0–2.0 cun.
EX‐HN5 (Taiyang)	On the lateral face of the head. This acupoint is found in the depression one fingerbreadth (middle finger) posterior to the midpoint between the medial end of the eyebrow and the lateral canthus of the eye.	The needle is inserted vertically by 0.3–0.5 cun.
LU7 (Lieque)	On the lateral side of the forearm. This acupoint is found 1.5 cun superior to the palmar wrist crease, between the tendons of the abductor pollicis longus and the extensor pollicis brevis muscles, in the groove for the abductor pollicis longus tendon.	The needle is inserted obliquely upward by 0.3–0.5 cun.
SP6 (Sanyinjiao)	On the medial aspect of the leg. This acupoint is found 3 cun above the medial malleolus, at the back edge of the tibia.	The needle is inserted vertically by 1.0–1.5 cun.
LI4 (Hegu)	On the dorsum of hand. This acupoint is found radial to the midpoint of the second metacarpal bone.	The needle is inserted vertically by 0.5–1.0 cun.
ST8 (Touwei)	On the head. This acupoint is found 0.5 cun directly superior to the anterior hairline at the corner of the forehead, 4.5 cun lateral to the anterior median line.	The needle is inserted horizontally by 0.5–0.8 cun.
LR3 (Taichong)	On the dorsum of the foot. This acupoint is found between the first and second metatarsal bones, in the depression distal to the junction of the bases of the two bones, over the dorsal pedal artery.	The needle is inserted vertically by 0.5–1.0 cun.
PC 6 (Neiguan)	On the inner side of the forearm. This acupoint is 2 cun above the wrist crease, positioned between the tendons of the palmaris longus and flexor carpi radialis.	The needle is inserted vertically by 0.5–1.0 cun.
GB8 (Shuaigu)	On the head directly superior to the auricular apex. This acupoint is found 1.5 cun superior to the temporal hairline.	The needle is inserted horizontally by 0.5–0.8 cun.
GB34 (Yanglingquan)	On the fibular aspect of the leg. This acupoint is found in the depression anterior and distal to the head of the fibula.	The needle is inserted vertically by 1.0–1.5 cun.
SI3 (Houxi)	On the dorsum of the hand. This acupoint is found in the depression proximal to the ulnar side of the fifth metacarpophalangeal joint, at the border between the red and white flesh.	The needle is inserted vertically by 0.5–1.0 cun.
BL9 (Yuzhen)	On the head. This acupoint is found 1.3 cun lateral to the posterior median line, at the same level as the external occipital protuberance.	The needle is inserted horizontally by 0.3–0.5 cun.

**FIGURE 2 fig-0002:**
[figure not shown]
Acupoint location for the electroacupuncture and sham electroacupuncture groups. GV20: Baihui; GV24: Shenting; ST8: Touwei; GB8: Shuaigu; EX‐HN5: Taiyang; BL9: Yuzhen; LU7: Lieque; LI4: Hegu; SI3: Houxi; PC6: Neiguan; CV4: Guanyuan; GB34: Yanglingquan; SP6: Sanyinjiao; LR3: Taichong.

#### 2.3.2. Sham Electroacupuncture Group

Participants in the sham electroacupuncture group will be treated with sham acupuncture at the same acupoints as those in the electroacupuncture group. To fix the needle, the adhesive pads will be attached to the acupoints, and blunt needles without a sharp tip (Guizhou Andi Medical Equipment Co.) were passed through the pad to reach the skin surface, without skin breakage or Deqi sensation. The sham acupuncture device used above has been patented by the China National Intellectual Property Administration (Patent Number: ZL 2023 2 0605629.3). Additionally, a specialized power line that is disrupted with a normal appearance (the electric needle instrument shows the on state, but it is not actually powered on) connects the same acupoints as those in the electroacupuncture group. The needle retention time, treatment frequency, and treatment duration will be the same as those in the electroacupuncture group.

## 3. Outcomes

At baseline, basic information about the participants will be collected, including age, body mass index (BMI), duration of migraine, accompanying symptoms of migraine (nausea, vomiting, photophobia, and phonophobia), and medication history. A 28‐week headache diary needs to be kept (including a 4‐week baseline period, 12‐week treatment period, and 12‐week follow‐up period). The headache diary will record daily frequency, time, location, VAS score, and associated symptoms of migraine as well as medications taken and menstrual periods. The schedule of enrollment and assessment is shown in Table 2.

**TABLE 2 tbl-0002:** Schedule of enrollment, interventions and assessments.

Study period		Enrollment	Intervention period			Follow‐up period
Time point		Weeks −3–0	Weeks 1–4	Weeks 5–8	Weeks 9–12	Weeks 13–24

Eligibility screening		×				

Sign informed consent		×				

Medical history		×				

Randomization		×				

Intervention						

Electroacupuncture			×	×	×	

Sham electroacupuncture			×	×	×	

Primary outcomes (vs. baseline)						

Migraine days and attacks during Weeks 9–12					×	

Secondary outcomes (vs. baseline)						

Frequency‐related	Migraine days/attacks per 4 weeks (Weeks 1–24, excluding Weeks 9–12)		×	×		×
	Migraine days/attacks per 4 weeks (during menstrual/nonmenstrual periods)	×	×	×	×	×

Symptom characteristics	Days/attacks with migraine‐associated symptoms, and attack duration per 4 weeks	×	×	×	×	×

Patient‐reported	VAS	×	×	×	×	×
	MIDAS	×			×	
	ISI	×			×	
	GAD‐7	×			×	
	PHQ‐9	×			×	

Others	Treatment response rate (the proportion of patients with ≥ 50%, 75%, or 100% reduction per four weeks of migraine days)		×	×	×	×
	Average dosage and frequency of emergency drugs	×	×	×	×	×

Adverse events			×	×	×	×

Success of blinding					×	

### 3.1. Primary Outcome

The primary outcome was migraine days and attacks during Weeks 9–12 vs. baseline. Data were recorded in a headache diary.

### 3.2. Secondary Outcomes (All vs. Baseline Unless Specified)

The secondary outcomes included the following:1.Frequency‐related: migraine days/attacks per 4 weeks (Weeks 1–24, excluding Weeks 9–12; and during menstrual/nonmenstrual periods).2.Symptom characteristics: days/attacks with migraine‐associated symptoms (nausea, vomiting, photophobia, and phonophobia) and attack duration per 4 weeks.3.Patient‐reported: (a) VAS: The VAS score is derived from the headache diary, which will be evaluated during the 4‐week baseline period and Weeks 1–24. (b) MIDAS [25]: This is a questionnaire used to assess the degree of migraine‐related disability and reflect the severity of migraine. The questionnaire is simple and effective and has been widely recognized and accepted by scholars worldwide. It was translated into Chinese in 2006 and has good test–retest reliability and validity. This will be evaluated at Weeks 0 and 12. (c) Insomnia Severity Index (ISI) [26]: It evaluates the severity of subjective insomnia in patients over the past week, including seven items, each with 0–4 points. The higher the score, the more serious the degree of insomnia. This will be evaluated at Weeks 0 and 12. (d) Generalized Anxiety Disorder‐7 (GAD‐7) (Copyright 1999 Pfizer Inc., all rights reserved) [27]: This scale is commonly used to evaluate generalized anxiety disorder. The scale evaluates the frequency and severity of anxiety symptoms in the past 2 weeks through seven questions. This will be evaluated at Weeks 0 and 12. (e) Patient Health Questionnaire‐9 (PHQ‐9) (Copyright 1999 Pfizer Inc., all rights reserved) [27]: It is a simple and effective self‐rating scale for assessing whether individuals have depressive symptoms and their severity. It consists of nine questions covering common symptoms of depression. This will be evaluated at Weeks 0 and 12.4.Others: treatment response rate (the proportion of patients with a reduction of ≥ 50%, 75%, or 100% per four weeks migraine days compared with baseline [28]), average dosage, and frequency of emergency drugs.

The above data regarding MRM days, attacks, duration, associated symptoms, VAS scores, and usage of remedial drugs were all derived from the headache diary. The participants will be required to complete a headache diary for at least 20 of the 28 days [29].

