The clinical efficacy of acupuncture in the treatment of migraine has been substantiated in numerous RCTs [32]; however, related research is limited regarding its effectiveness, specifically for MRM. This study was designed to address the unique characteristics of MRM and proposes an EA intervention. MRM is closely linked to the menstrual cycle, particularly during premenstrual and menstrual phases. Accordingly, our intervention included two treatments in the premenstrual and menstrual weeks, along with one treatment in each of the other 2 weeks. This approach not only enhances the specificity of treatment but also reduces the time burden on patients. The location of migraine attacks is another critical factor in electroacupuncture treatment. Thus, during acute migraine phases, supplementary acupoints are chosen based on the location of pain to optimize treatment effectiveness. In addition to acupoint selection, the choice of electrical stimulation parameters is equally important. Previous studies have shown that alternating stimulation at 2 and 100 Hz using a sparse‐dense wave can simultaneously activate the enkephalin and dynorphin systems, producing a stronger synergistic analgesic effect than single‐frequency stimulation [33]. Furthermore, a randomized controlled trial involving 90 patients with migraine confirmed that variable‐frequency (2/100 Hz) electroacupuncture exhibited superior clinical efficacy compared with low‐frequency (2 Hz) or high‐frequency (100 Hz) electroacupuncture in the treatment of migraine [34]. Taken together, these findings provide a solid physiological and clinical rationale for using the 2/100 Hz alternating sparse‐dense wave protocol in the present trial. Furthermore, to bolster the reliability of our study, both electroacupuncture and sham electroacupuncture treatments will utilize the same auxiliary device (patent number: ZL 2023 20605629.3). This strategy not only facilitates blinding but also encourages patient adherence to treatment. Previous clinical studies have confirmed the feasibility of placebo application [35].

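### ISI and GAD-7 see only one or two weeks of the cycle and are compared by an unadjusted test, which costs some precision, without bias, when cycles are not 28 (or 21) days long

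*Protocol article*

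**What the plan says.** All places are in the protocol article.

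- **Recall, Section 3.2.** For the ISI: "It evaluates the severity of subjective insomnia in patients over the past week, including seven items, each with 0–4 points". For GAD-7: "The scale evaluates the frequency and severity of anxiety symptoms in the past 2 weeks through seven questions".
- **Timing, Section 3.2.** For both scales: "This will be evaluated at Weeks 0 and 12". Table 2 agrees, with one mark at enrollment and one under Weeks 9–12. No cycle day is attached to either assessment.
- **Cycle, Section 2.2.** The criterion is "with regular menstrual cycle", with no range of lengths.
- **Disease pattern.** Section 9 says "MRM is closely linked to the menstrual cycle, particularly during premenstrual and menstrual phases". The Introduction links migraine to anxiety, depression and insomnia.
- **Use of the cycle elsewhere.** Treatment follows it (Section 2.3: "twice a week in the week before and during the menstrual period, once a week for the remaining 2 weeks"). Migraine days and attacks are also split into menstrual and nonmenstrual periods (Section 3.2).
- **Data available, Section 3.** The diary covers symptoms "as well as medications taken and menstrual periods".
- **Analysis, Section 7.** Quantitative secondary outcomes are compared by two-sample t-test or rank-sum test. Repeated measurements go to generalised estimating equations, without saying which outcomes these are. No phase term is named. The covariate analyses mentioned in Section 9 concern emergency medication.

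**The concern.** The diary outcomes are counted over four weeks, about one full cycle, so phase largely averages out. The ISI sees 7 of 28 days (25%) and GAD-7 sees 14 of 28 (50%). Whether a score covers a migraine-prone or a quiet stretch then depends on where in her cycle the woman is at the visit. If that differs between Weeks 0 and 12, her change from baseline contains a phase component unrelated to treatment. An unadjusted test leaves this component in the error term. What is at stake is the precision of two secondary comparisons, and the reading of individual or single-arm changes.

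**Working it through.** The article gives no figure for the variance of ISI or GAD-7, so there is none to reproduce. Its sample size rests on migraine days and attacks and does not bear on this point.

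**Inputs from the article.** Recall windows of 7 and 14 days; assessments 12 × 7 = 84 days apart; regular cycles of unspecified length.

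**Assumed inputs.** Scores higher by A = 2 or 3 points over 14 peri-menstrual days (the week before and the week of menses); residual SD of the change 5; starting phase uniform; cycle lengths equally likely over 26–30 or 24–35 days.

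**1. Phase shift and overlap.** For cycle length L, shift d = min(84 mod L, L − 84 mod L). For a window of w days, overlap = [max(0, w − d) + max(0, w − (L − d))] / w, capped at 1. The second term allows for the window wrapping round the cycle.

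| Cycle length (days) | Shift (days) | ISI overlap | GAD-7 overlap |
|---|---|---|---|
| 28 (also 21) | 0 | 100% | 100% |
| 27 or 29 | 3 | 4/7 = 57% | 11/14 = 79% |
| 26 or 30 | 6 | 1/7 = 14% | 8/14 = 57% |
| 24 | 12 | 0 | (2 + 2)/14 = 29% |
| 32 | 12 | 0 | 2/14 = 14% |
| 35 | 14 | 0 | 0 |

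**2. Bias.** Let f0 and f12 be the peri-menstrual shares of the recall window at Weeks 0 and 12. A woman's change is the treatment effect (if treated) + A(f12 − f0) + error. Starting phase and usual cycle length are fixed before randomisation, so the mean of f12 − f0 is the same in both arms and cancels. A simulation of the two-arm t-test (51 per arm) agreed: bias was below 0.01 SD and type I error 4.3–5.6%.

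**3. Added variance.** This is A² × E[(f12 − f0)²], averaged over every starting day and each whole-day cycle length.

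| Scale, cycle range | E[(f12 − f0)²] | A = 2 | A = 3 | Rise over 5² = 25 |
|---|---|---|---|---|
| ISI, 26–30 d | 0.139 | 0.56 | 1.25 | 2–5% |
| ISI, 24–35 d | 0.393 | 1.57 | 3.53 | 6–14% |
| GAD-7, 26–30 d | 0.067 | 0.27 | 0.60 | 1–2% |
| GAD-7, 24–35 d | 0.212 | 0.85 | 1.91 | 3–8% |
| Either, 28 d | 0 | 0 | 0 | 0 |

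If the effect is confined to a 7-day block, the ISI figures for 24–35 days fall to 0.91 and 2.04, or 4–8%.

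**4. Power, under a different set of assumptions.** With a 7-day block, cycles of 24–32 days or fully random phase, and a true effect of 0.65 SD, power starts at about 90%. A phase effect of 0.5 SD takes it to about 88–89% for ISI and 89–90% for GAD-7. A phase effect of 1 SD takes it to about 85% and 88%.

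**5. Gain from adjustment.** With correlation r between the two scores, ANCOVA on baseline has a standard error √((1 + r)/2) times that of the change-score test. At an assumed r = 0.5 this is √0.75 = 0.87, or 13% lower. Simulation with baseline and phase covariates, under assumed effects, gave a reduction of about 12–19%, mostly from the baseline score.

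**The case against.** The strongest objection is that this rests on silence in a condensed article. Visit windows, the rule that starts Week 1 and covariate lists may be in the full protocol. That stands in part: if the full protocol ties these visits to the cycle, most of the variance component disappears. But the article does state the visit weeks and does name the test, and the named test uses neither baseline as a covariate nor phase.

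The size is also open to challenge. No phase effect or SD for these scales is in the article. Equal weight on every length from 24 to 35 days is generous, and 84 days is exactly three 28-day cycles. This stands, and the narrower 26–30 day range is therefore given equal prominence.

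A reader might go further and infer that the change score confounds treatment with cycle phase. The article does not support that. The comparison is between concurrent randomised arms, and phase is balanced in expectation. A woman with a menstrual baseline and a mid-cycle Week 12 score can appear to improve without treatment, but within-woman change is not the stated inference.

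Moving Week 12 questionnaires to match cycle day would be a doubtful remedy. It could shift some by up to about two weeks, vary the time since the last session and push some into follow-up. Adjusting for observed Week 12 phase has its own weakness, because that phase is measured after randomisation.

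**Conclusion.** The point holds as a minor one about precision. The short recall windows, the fixed 84-day gap, the open cycle length and the unadjusted test together leave avoidable variance in the ISI and GAD-7 comparisons. The rise is about 2–5% for ISI with cycles of 26–30 days and 6–14% with 24–35 days, about half that for GAD-7, and zero at 28 days. These figures depend on the assumed 2–3 point phase effect, the residual SD of 5 and the assumed spread of cycle lengths. There is no bias in the randomised comparison and no inflation of type I error. The primary outcome is not affected. PHQ-9 shares the visits, but the article gives no recall period for it, so nothing is claimed there.

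**What to change.** In Section 7, replace the unadjusted test for these two scales with an ANCOVA of the Week 12 score on treatment arm, the Week 0 score, and the share of each recall window that is premenstrual or menstrual. Derive the shares from the diary's menstrual dates and state which days count as premenstrual.

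For Week 12, use the phase predicted from baseline cycle dates as the primary covariate, since it cannot be affected by treatment. Use the phase observed in the diary as a sensitivity analysis. Fix this before unblinding. Leave the Week 12 visit where it is.

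The cost is two covariates beyond the baseline score and some derivation work. A 28-day baseline diary will often contain only one menstrual onset, so the prediction may also need each woman's usual cycle length from her history. Most of the gain in precision comes from the baseline score, so that term is worth adding even if the phase terms are judged not worth the effort.
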